**Figure 2 F2:**
[figure not shown]
Patient and carer data collection flow chart for both intervention and control groups, * indicates data collection points.

#### Data analysis

The main hypothesis will be tested using logistic regression controlling for baseline values and cluster using robust standard errors. Achieving preferred place of death will be presented as odds ratios, for control and intervention periods with associated 95% confidence intervals. A secondary analysis will explore last stated preferred place of death versus actual place of death using a similar approach.

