### Randomisation

The rapid response service will be rolled out sequentially in the three centres with six months between the start of provision in each site (Figure 1). A simple probabilistic randomisation method will be used to determine the order in which the three areas start the rapid response service. Once the intervention is introduced in an area, it will be available to all patients within the catchment area of that hospice, while usual services will continue to be offered in the control areas until the new service is rolled out in that area.

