**Figure 1 F1:**
[figure not shown]
Time of service delivery by area.

The evaluation design randomises centres and therefore does not require the blind randomisation of individual patients into intervention or control group which would create serious ethical and practical problems. It is a design that protects from a number of potential sources of bias: contamination between patients, changes in health policy over time and resentful demoralisation of patients [11]. The design simultaneously addresses the situational and resource factors that arise from implementing an intensive new service across a wide area.

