#### Data analysis

Prior to the analysis of outcomes distributional assumptions will be checked and the analytical framework adjusted to account for these. Analysis of quality of life will be conducted using analysis of covariance, or non-parametric equivalent, adjusting for baseline values and carer burden. Potential cluster effects will be explored using robust standard errors. A similar approach will be employed for other carer outcomes. Results will be presented as means per group and appropriate estimates of precision.

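### The primary model has no calendar-period term although the service is phased in over time, so part of any secular trend would be attributed to the service

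*Protocol article*

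**What the plan says.** The Randomisation section of the protocol article describes the roll-out: "The rapid response service will be rolled out sequentially in the three centres with six months between the start of provision in each site". Only the sequence is random: "A simple probabilistic randomisation method will be used to determine the order in which the three areas start the rapid response service". Movement is in one direction: "usual services will continue to be offered in the control areas until the new service is rolled out in that area". The patient Sample size section builds the study on nine site-by-six-month cells of 49 patients, 441 in all.

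The text under Figure 1 claims that this arrangement guards against calendar effects: "It is a design that protects from a number of potential sources of bias: contamination between patients, changes in health policy over time".

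The Data analysis section of the patient evaluation names the adjustment terms of the primary model: "The main hypothesis will be tested using logistic regression controlling for baseline values and cluster using robust standard errors". The contrast is then reported this way: "Achieving preferred place of death will be presented as odds ratios, for control and intervention periods with associated 95% confidence intervals". The secondary analysis of last stated preference is to follow a similar approach.

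For carers the model is: "Analysis of quality of life will be conducted using analysis of covariance, or non-parametric equivalent, adjusting for baseline values and carer burden". Robust standard errors are to be used to explore clustering. Neither section names a period or time term.

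**The concern.** In a one-way phased roll-out, exposure to the service rises with calendar time. Randomising the order of the centres makes the sequence fair between centres, but it does not balance intervention and control over time. Protection against a trend comes from comparing the two within the same six-month period, and the stated model does not do that. Robust standard errors alter the estimated precision and leave the bias untouched.

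The article gives reasons to take a trend seriously, though no measure of one. The Background cites national policy guidance that stresses patients' wishes on place of death. The Discussion mentions a planned early effort to help staff record preferences. Deaths without a recorded preference are excluded, so a change in recording could change who is analysed from one period to the next.

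At stake are the primary odds ratio and its type I error. The economic evaluation is also affected, because its cost per percentage point gained uses the between-group difference in the primary outcome.

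**Working it through.** **Inputs.** From the patient Sample size section: 29% under usual care, 60% as target, two-sided alpha 0.05, 90% power, 49 per cell, 9 cells, 441 in total. From Randomisation: three centres, starts six months apart. Trend sizes are assumptions.

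**The plan's own figure.** (1.96 + 1.2816)² x (0.29 x 0.71 + 0.60 x 0.40) / 0.31² = 48.8, so 49; 49 x 9 = 441. The figure reproduces and is not in dispute.

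**Layouts.** Figure 1 is not shown, so both 3 x 3 layouts that fit the text were checked (rows are sites, columns are periods, 1 = service):
- A, first site starts in period 1: 111 / 011 / 001 (6 service cells, 3 control).
- B, common control period first: 011 / 001 / 000 (3 service cells, 6 control).

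Both give the same results below.

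**Service against time.** Code period as t = -1, 0, 1.
- Sum of service x t over the cells = 2. Sum of t² = 6.
- Residual sum of squares (RSS) of the service indicator: 2 pooled; 4/3 after site; 2/3 after site and period.
- Correlation of service with period = 2 / √(2 x 6) = 0.58.

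**Bias from a linear trend of x points per period** = (sum of service residual x t) / RSS:
- pooled: 2 / 2 = 1.0x;
- site terms: 2 / (4/3) = 1.5x;
- site and period terms: 0.

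The total rise from period 1 to period 3 is 2x, so the share credited to the service is one half (pooled) or three quarters (site terms).

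**Type I error with no true effect, linear approximation, independent patients.** SE = √(0.247 / (49 x RSS)), where 0.247 = 0.445 x 0.555 is the variance at the mean of 29% and 60%. This gives 0.0502 pooled and 0.0615 with site terms.

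| Assumed trend | Model | False effect | Bias / SE | Type I error |
|---|---|---|---|---|
| 3 points | pooled | 3.0 points | 0.60 | 9% |
| 3 points | site | 4.5 points | 0.73 | 11% |
| 5 points | pooled | 5.0 points | 1.00 | 17% |
| 5 points | site | 7.5 points | 1.22 | 23% |

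That variance suits a mixture of 29% and 60% better than a no-effect scenario. If the rate instead runs 29%, 34%, 39%, the variance at its mean is 0.34 x 0.66 = 0.2244. The SEs become 0.0479 and 0.0586, and the errors at 5 points become 18% and 25%.

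**Check on the logistic scale.** Simulation of binomial logistic models (1,500 runs per scenario, 49 per cell, model-based standard errors, no service effect) gave:
- no trend: odds ratio (OR) 1.00, error about 5%;
- 3 points: OR 1.15 pooled or 1.23 with site, error 9-11% or about 11-12%;
- 5 points: OR 1.25 or 1.40, error 18-20% or 25%.

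The ORs at 5 points agree with the shares above. The log-odds rise from 29% to 39% is 0.448; exp(0.448 / 2) = 1.25 and exp(0.75 x 0.448) = 1.40.

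**With site and period terms.** The simulated OR under a pure trend returns to 1.00 and the false-positive rate to about 4.5-6.6%. SE = √(0.247 / (49 x 2/3)) = 0.0870, so power for 31 points is Φ(0.31 / 0.0870 - 1.96) = Φ(1.60), about 95%. Simulation gave about 94% (layout A) and 93% (layout B).

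**The case against.** The strongest defence is that this is a condensed article with a one-sentence model, and full covariate lists are commonly left to the analysis plan. That limits any confidence that the final analysis will omit period. It does not dispose of the point: the article names its adjustment terms, and those terms do not support the unqualified claim of protection from changes over time.

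Some stronger readings should be resisted.
- A reader might infer that a trend would be counted in full as a service effect. It would not. Some usual-care cells run alongside service cells, so under a linear trend the share is about half to three quarters. The bias also takes the sign of the trend, so it need not favour the service.
- A reader might infer that the article shows a trend. It does not. The Background says that guidance stresses patients' wishes, and the Discussion says that help with recording was planned. Neither gives a change in the rate of achieving the preference. The 3 and 5 points are assumptions, and a false effect of 5 to 7.5 points is about a sixth to a quarter of the planned 31-point difference.
- A reader might infer that baseline values can mean nothing here, because each patient dies once. The phrase may mean patient characteristics at intake, or a site-level rate from the baseline data collection period mentioned in the Discussion. It is loose, but neither reading adjusts for calendar time.
- The error rates are not those of the exact planned test. Robust standard errors with three centres may not start from 5%.
- For carers there is no calculated bias, and each carer's own baseline score may absorb some drift in level. That part is secondary.

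**Conclusion.** The concern stands in this form: service exposure is correlated with calendar time (about 0.58), the stated primary model does not adjust for time, and so part of any secular trend is attributed to the service. Under a linear trend that part is about half of the period 1-to-3 rise in a pooled model and three quarters with site terms; an adverse trend would mask a benefit. Randomising the order of roll-out does not remove this unless the analysis compares within period.

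The size depends on a trend that the article does not give. With no true effect, independent patients and 49 per cell, an assumed 5 points per period produces a false effect of 5 to 7.5 points and a type I error of roughly 17-25%. An assumed 3 points produces 3 to 4.5 points and roughly 9-12%. With no trend there is no bias. The result is the same in both layouts, so it does not depend on the missing figure. Because the primary estimate is affected and the remedy needs no new data, it should be corrected before analysis.

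**What to change.** Specify the primary model, and the secondary last-preference model, as logistic regression on the service indicator with fixed effects for site (3 levels) and six-month calendar period (3 levels). Define period on the same time axis that assigns patients to control or intervention. The article enters patients at first assessment but restricts the analysis to deaths within the control or intervention period, so the rule for patients who span two periods should be written down. State whether the robust standard errors are kept.

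Say which baseline patient characteristics the term baseline values covers, for example the diagnosis and demographic data already being extracted. As a secondary point, add the same site and period terms to the carer analysis of covariance.

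The change is to the analysis wording only. The price is precision: the variance of the service effect doubles against a site-only model (RSS falls from 4/3 to 2/3), so its standard error rises by about 41%. Power for 29% v 60% with 441 patients falls from more than 99% without period terms to about 93-95%, still above the planned 90%, provided patients are independent and there is no extra site-by-period variation.

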#### Sample size

The primary outcome measure for the patient evaluation is death in the first recorded preferred place of death. In current 'usual' service provided by Pilgrims Hospices, approximately 29% of patients die in their preferred place of death. Increasing this figure to 60% will be equivalent to the gold standard framework for end of life care. In order to detect a difference of this magnitude, with alpha at 0.05 and 90% power, using a 2-sided test, requires data to be collected on 49 new patients per site per six month period. The design of the study involves 9 cells (Figure 1) so the total sample size is inflated to 441. This equates to 147 for each of the three sites and 147 for each six monthly period.

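### Robust standard errors clustered on three centres do not hold the primary test at 5%, even if patients are independent

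*Protocol article*

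**What the plan says.** Under Randomisation, the service starts in one centre after another: "The rapid response service will be rolled out sequentially in the three centres with six months between the start of provision in each site". Chance enters only through the order: "A simple probabilistic randomisation method will be used to determine the order in which the three areas start the rapid response service". The text beside Figure 1 confirms the unit: "The evaluation design randomises centres and therefore does not require the blind randomisation of individual patients".

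The patient Data analysis section fixes the primary test as logistic regression "controlling for baseline values and cluster using robust standard errors". The result is to be reported with an interval: "Achieving preferred place of death will be presented as odds ratios, for control and intervention periods with associated 95% confidence intervals". The carer Data analysis section uses the same device more tentatively: "Potential cluster effects will be explored using robust standard errors".

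The patient Sample size section sets two-sided alpha at 0.05 and 90% power for 29% versus 60%, with 49 patients in each of nine site-by-period cells. It has no term for clustering. The article names no reference distribution and no correction for few clusters.

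**The concern.** The cluster sandwich variance is justified as the number of independent clusters grows. Here it would be built from three centre score totals. With an intercept in the model these sum to zero, so at most two independent pieces of information estimate the variance. The estimate is biased downwards and very unstable, and recruiting more patients per centre does not help.

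The primary p-value and interval depend on it. The economic section then makes a significant improvement at lower cost the condition for preferring the new service, so a test that rejects too often feeds directly into a commissioning conclusion.

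**Working it through.** **The plan's own figure.** Two proportions, unpooled variance:

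n = (1.960 + 1.282)² × (0.29 × 0.71 + 0.60 × 0.40) / 0.31² = 10.507 × 0.4459 / 0.0961 = 48.75, so 49 per cell; 49 × 9 = 441.

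The stated numbers reproduce. They treat patients as independent.

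**Type I error of the planned test.** Inputs from the article: 3 sites, 3 six-month periods, 49 patients per cell, alpha 0.05. Assumptions:
- no treatment effect;
- true rate 29%, or the midpoint (29 + 60)/2 = 44.5%;
- between-site and between-cell SDs from 0 to 5 percentage points, or similar values on the logit scale;
- because Figure 1 is not shown, two roll-outs: first centre starting in period 1, or in period 2 after a common baseline.

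Each setting had 2,000 to 4,000 simulated trials, so the Monte Carlo standard error is about 1 point or less, for example √(0.25 × 0.75/2000) = 0.010. With G = 3 the factor G/(G-1) is 1.5. The t critical value on 2 df is 4.30, against 1.96 for the normal.

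| Model, errors clustered on 3 centres | No factor, normal | G/(G-1), normal | G/(G-1), t on 2 df |
|---|---|---|---|
| Treatment only | 30–33% | 23–26% | 6–8% |
| Plus site | 37–41% | 32–35% | 15–18% |
| Plus site and period | 36–40% | 29–33% | 9–11% |

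A model with period terms but no site terms was slightly worse (up to 44% without the factor, 36% with it). The inflation is there with no between-site or between-cell variation at all and hardly changes over the assumed range, so it does not rest on a guessed intracluster correlation. The median uncorrected robust standard error was 0.40 to 0.56 of the true SD of the estimate. Coverage of the nominal 95% interval was about 75 to 76% where computed (treatment-only model, G/(G-1), normal reference).

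**The other reading.** With centre as a covariate and patient-level robust errors, type I error is about 5% when cells vary only binomially, 7 to 8% at a between-cell SD of 3 points and 11 to 13% at 5 points. Model-based errors with site and period terms behave the same way.

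**An analysis that holds its level.** Regress the nine cell proportions on treatment, site and period. Parameters: 1 + 1 + 2 + 2 = 6, leaving 9 − 6 = 3 df. Type I error was about 4 to 6% in every setting.

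Power at 29% versus 60%: in both roll-outs the treatment coefficient has variance 1.5 times the variance of one cell proportion.
- SE = √(1.5 × 0.445 × 0.555 / 49) = 0.087
- Noncentrality = 0.31 / 0.087 = 3.57
- Critical t on 3 df = 3.18, giving power of about 0.67

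Using the average of the two arms' binomial variances instead, (0.2059 + 0.2400)/2 = 0.2230, gives SE 0.083 and power of about 0.71. With a normal reference the first noncentrality would give about 0.95, so the loss comes almost entirely from having 3 df.

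**The case against.** **The wording allows another reading.** Centre could be a covariate, with robust errors at patient level. The largest inflation figures then disappear, and the plan differs from the proposed model mainly in lacking period terms. This stands as a condition on the size of the problem. The carer section, which ties cluster effects explicitly to robust errors, makes the cluster-robust reading the natural one but does not settle it.

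**The article states no critical values.** A reader might infer that normal critical values are planned; the article does not say so, and an unseen analysis plan may name a correction. Two corrections were tested, G/(G-1) and t on 2 df, and together they leave 6 to 18%. Bias-reduced sandwich variances with Satterthwaite degrees of freedom and the wild cluster bootstrap were not tested, so it is not shown that every correction fails. Treating the nine cells as clusters still gave about 15% (normal) or 10% (t on 8 df) in the treatment-only model.

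**The carer tests.** A reader might extend the same inflation to them. That is not supported: no carer simulation was run, the planned method is analysis of covariance or a non-parametric equivalent, and the section promises only to explore cluster effects.

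**The randomisation itself.** Three centres give 3! = 6 orders, so no randomisation-based p-value can fall below 1/6. This is a limit of the design that no analysis wording removes, and the article already calls the study quasi-experimental.

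**The model-based remedy is not safe alone.** This is right. Once cells vary by 5 points it does no better than a sandwich with G/(G-1) and t on 2 df (about 9 to 10% with site and period terms). That is why the 3-df analysis has to carry weight in the conclusion.

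**Conclusion.** The concern holds, with its size depending on the reading. With errors clustered on three centres, a nominal 5% primary test rejects a true null in about 23 to 35% of trials with G/(G-1) and a normal reference, 30 to 41% without the factor, and about 6 to 18% with the factor and t on 2 df. The 95% intervals are correspondingly too narrow. With centre as a covariate and patient-level robust errors, the level is about right if cells vary only binomially and 11 to 13% at a cell SD of 5 points.

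The cluster-robust result rests on three centres, the nine-cell layout and 49 patients per cell, all from the article. The site and cell SDs are assumptions and matter mainly for the milder reading. The size of any carer inflation is not computed.

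**What to change.** In the patient Data analysis section:
- Remove the sandwich errors clustered on three centres.
- Fit logistic regression with site and period fixed effects and model-based standard errors.
- Pre-specify the same treatment contrast from the nine site-period proportions, with a t reference on 3 df.
- Claim effectiveness only if the 3-df analysis supports it.

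In the carer Data analysis section, state that inference will not rely on robust errors from three clusters.

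The change is to wording and analysis only. The price is wider intervals and lower power: about 67% for the 3-df analysis at 49 per cell when cells vary only binomially, and less if they vary more. The stated 90% should be read in that light. The hospice's roughly 2,000 referrals a year (2,000/3/2 = 333 per site per six months) should not be cited as an offset, because only patients who die in the study period with a recorded preference are analysed, and that number is not given.

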#### Economic evaluation for patients

A critical aspect of an evaluation such as this is to include a measure of impact from an economic perspective particularly one that could be utilised by commissioners to make decisions regarding the relative economic impact of an intervention. The costs of the intervention will be calculated on an individual patient basis. Staff time input, mileage travelled to patient homes and consumables used in the delivery of the rapid response intervention will be obtained from the service’s activity logs and patient records. Resource utilisation will be converted to costs using nationally validated unit costs, for staff time [13], and information from local financial managers for expenditure on travel and consumable items. The overall service utilisation of all participants during the time they are in the study will be collected for all patients in both arms including: general practice and community resources, outpatient, inpatient stays, out of hours service, Marie Curie nurse visits, and social care packages. This information will be gathered from providers’ databases for the period that each patient is in the study, and converted to unit costs [13]. The extent to which the rapid response service substitutes for other forms of health and social care (both community-based and inpatient) will be assessed.

The difference between the mean cost of patients in the rapid response arm and patients receiving treatment as usual will be calculated and compared with the difference between groups in the primary effectiveness outcome (proportion dying in preferred place of death). If the hospice intervention results in significantly improved outcomes at lower cost, it becomes the service delivery option of choice. If the intervention achieves superior outcomes (significantly more patients dying in their preferred place), but at higher cost, the cost per percentage point gain in dying in the preferred place will be calculated.

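### The primary effect is specified as an odds ratio, but the target and the cost rule need percentage points; that difference is not tied to the adjusted model, and no calendar-period term is named for either

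*Protocol article*

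**What the plan says.** All places are in the Protocol article.

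- **Patient evaluation, Sample size.** The trial is planned on an absolute change. Under usual service "approximately 29% of patients die in their preferred place of death", and "Increasing this figure to 60% will be equivalent to the gold standard framework for end of life care".
- **Same section, layout.** "The design of the study involves 9 cells (Figure 1) so the total sample size is inflated to 441", and "This equates to 147 for each of the three sites and 147 for each six monthly period". This implies three sites by three six-month periods with equal cells.
- **Patient evaluation, Data analysis.** "The main hypothesis will be tested using logistic regression controlling for baseline values and cluster using robust standard errors". The next sentence gives the effect measure: "Achieving preferred place of death will be presented as odds ratios, for control and intervention periods with associated 95% confidence intervals". Calendar period is not among the named terms.
- **Economic evaluation for patients.** The difference in mean cost is set against the between-group gap in the proportion dying in the preferred place. If outcomes are significantly better at higher cost, "the cost per percentage point gain in dying in the preferred place will be calculated". The section does not say whether that gap comes from the model or from simple proportions, and it names no adjustment for the cost difference.
- **Randomisation.** The service starts in the three centres one after another, six months apart. The design is said to protect against changes in health policy over time.

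**The concern.** The adjusted analysis is specified on a scale that neither the planning target nor the cost rule can use directly. The cost rule applies when the improvement is significant, and the main hypothesis is tested with the logistic model. The size of the gain is then described separately, as a difference in proportions. One decision rule could thus take its significance from one estimate and its size from another, and the two can disagree.

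This matters more than usual because of the staggered start. Intervention experience falls later in calendar time than control experience, and sites contribute unequally to the two conditions. A simple pooled difference mixes the service effect with any drift in outcomes and with site differences. The design can protect against policy change over time only if the analysis compares like periods with like. Commissioners are the stated audience for the cost figure, so an error in its denominator bears directly on the decision.

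**Working it through.** **1. The plan's own figure.** Inputs from Sample size: p1 = 0.29, p2 = 0.60, two-sided alpha 0.05, power 90%. With unpooled variance:

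n = (1.960 + 1.282)² × [0.29 × 0.71 + 0.60 × 0.40] / 0.31² = 10.507 × 0.4459 / 0.0961 = 48.75, rounded up to 49.

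Then 9 × 49 = 441 and 3 × 49 = 147. The stated figures reproduce, and they rest on an absolute difference of 31 points.

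**2. Odds ratio against percentage points.** The planned odds ratio is (0.60/0.40) / (0.29/0.71) = 3.67. The risk ratio is 0.60/0.29 = 2.07 and the risk difference is 31 points. The same odds ratio at other control rates gives:

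| Control rate | Gain in points |
|---|---|
| 20% | 27.9 |
| 29% | 31.0 |
| 40% | 31.0 |
| 50% | 28.6 |
| 60% | 24.6 |

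An odds ratio alone does not fix the points gained, although the spread is small near the stated 29%.

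**3. Timing of the cells.** Figure 1 is not shown, so two layouts are assumed, with periods numbered 1 to 3.

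- Starts in periods 1, 2 and 3: six intervention cells with mean period 2.33, three control cells with mean 1.33.
- Starts in period 2, in period 3 and after the study: three intervention cells with mean 2.67, six control cells with mean 1.67.

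The gap is 1.0 period in both. With equal cells, crude difference = true gain + one period of linear trend.

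**4. Effect on cost per point.** The trends are assumptions. For a given cost difference, cost per point relative to its true value is (true gain) / (true gain + trend).

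| Assumed trend per period | True gain 31: appears as | Cost per point | True gain 10: appears as | Cost per point |
|---|---|---|---|---|
| 2 points | 33 | 94% | 12 | 83% |
| 5 points | 36 | 86% | 15 | 67% |
| 10 points | 41 | 76% | 20 | 50% |

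**5. Does the odds ratio escape?** No. Take no service effect, a 29% start, 5 points per period and the first layout. The pooled control rate is 0.29 + 0.05 × 1/3 = 0.307 and the pooled intervention rate is 0.29 + 0.05 × 4/3 = 0.357. The odds ratio without a period term is (0.357/0.643) / (0.307/0.693) = 1.25, where the truth is 1.

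**6. Which model removes the drift?** Logistic models were fitted to noise-free cell rates (29% start, no service effect, both layouts) and then standardised to a risk difference in points. The true value is 0.

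| Model terms beside treatment | Drift 3 | Drift 5 | Drift 10 |
|---|---|---|---|
| None (cluster only in the standard errors) | 3.0 | 5.0 | 10.0 |
| Site | 4.4 to 4.6 | 7.4 to 7.6 | 14.6 to 15.3 |
| Site and period | 0 | 0 | 0 |

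Site terms alone make it worse. In every site with both conditions, the intervention cells lie 1.5 periods after the control cells (for example, mean 2.5 against 1).

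**The case against.** The strongest reply is that nothing here is an error. An odds ratio is the natural output of a logistic model and gives a valid scale for testing the hypothesis. Planning on two proportions and testing by logistic regression is no contradiction. The economic section does name an absolute measure. How a model is turned into the increment of a cost ratio is often left to an analysis plan, and this is a condensed article. The trend sizes are assumed.

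Much of this stands, and it rules out several stronger readings:

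- A reader might infer that nothing but an odds ratio will be reported. The text names the odds ratio but does not exclude other measures.
- A reader might infer that the cost ratio will certainly use a crude difference. The economic section does not say so. That is its plain reading because no adjusted difference is named, but it remains a reading.
- A reader might infer that the odds-ratio scale causes the time confounding. It does not. The cause is the absence of a named period term, and the odds ratio shares the exposure (step 5).
- A reader might infer that converting the described model to a risk difference would be enough. Step 6 shows that it keeps the drift or enlarges it.

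What the reply does not remove is the mismatch between two stated choices. The adjusted effect is on one scale and the decision rule is on another, with no link between them. In a staggered design that link determines what the cost figure means.

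**Conclusion.** The point holds in a limited form. The primary effect is presented as an odds ratio, the target and cost rule are in percentage points, and the cost denominator is not tied to the adjusted model. Neither the effect analysis nor the cost comparison names calendar period.

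Taken at its plain reading, the denominator absorbs one full six-month period of any trend, plus site and case-mix differences. With an assumed trend of 2 to 10 points per period, cost per point would fall to between 94% and 76% of its true value if the true gain is 31 points, and to between 83% and 50% if it is 10. A falling trend would bias it the other way.

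This rests on three assumptions: one of the two 3 x 3 layouts with equal cells, a linear trend common to the sites, and a cost difference that is itself correct. The documents give no trend, so these figures show sensitivity and are not an estimate of bias. Choosing an odds ratio does not in itself undermine the hypothesis test.

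**What to change.** - **Patient evaluation, Data analysis.** Name calendar period (six-month period) and site as terms in the logistic model alongside the baseline values. Beside the odds ratio, report the risk difference obtained from that model by marginal standardisation, with a 95% confidence interval.
- **Economic evaluation for patients.** State that this site- and period-adjusted risk difference is the denominator of the cost per percentage point gained. Adjust the difference in mean cost for the same terms, so that numerator and denominator refer to the same comparison.

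The cost is a few more model terms, little extra analysis work and no new data. The interval will be somewhat wider, because in either assumed layout one of the three periods has all sites in the same condition and gives no within-period comparison.
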